# Efficacy of a Multimodal Digital Behavior Change Intervention on Lifestyle Behavior, Cardiometabolic Biomarkers, and Medical Expenditure: Protocol for a Randomized Controlled Trial

**DOI:** 10.2196/50378

**Published:** 2024-10-30

**Keywords:** health behavior, fitness, digital devices, lifestyle change, cardiovascular disease, chronic disease, physical activity, nutrition, sleep, mindfulness

## Abstract

**Background:**

The US Preventive Services Task Force recommends providers offer individualized healthy behavior interventions for all adults, independent of their risk of cardiovascular disease. While strong evidence exists to support disease-specific programs designed to improve multiple lifestyle behaviors, approaches to adapting these interventions for a broader population are not well established. Digital behavior change interventions (DBCIs) hold promise as a more generalizable and scalable approach to overcome the resource and time limitations that traditional behavioral intervention programs face, especially within an occupational setting.

**Objective:**

We aimed to evaluate the efficacy of a multimodal DBCI on (1) self-reported behaviors of physical activity, nutrition, sleep, and mindfulness; (2) cardiometabolic biomarkers; and (3) chronic disease–related medical expenditure.

**Methods:**

We conducted a 2-arm randomized controlled trial for 12 months among employees of an academic health care facility in the United States. The intervention arm received a scale, a smartphone app, an activity tracker, a video library for healthy behavior recommendations, and an on-demand health coach. The control arm received standard employer-provided health and wellness benefits. The primary outcomes of the study included changes in self-reported lifestyle behaviors, cardiometabolic biomarkers, and chronic disease–related medical expenditure. We collected health behavior data via baseline and quarterly web-based surveys, biometric measures via clinic visits at baseline and 12 months, and identified relevant costs through claims datasets.

**Results:**

A total of 603 participants were enrolled and randomized to the intervention (n=300, 49.8%) and control arms (n=303, 50.2%). The average age was 46.7 (SD 11.2) years, and the majority of participants were female (80.3%, n=484), White (85.4%, n=504), and non-Hispanic (90.7%, n=547), with no systematic differences in baseline characteristics observed between the study arms. We observed retention rates of 86.1% (n=519) for completing the final survey and 77.9% (n=490) for attending the exit visit.

**Conclusions:**

This study represents the largest and most comprehensive evaluation of DBCIs among participants who were not selected based on their underlying condition to assess its impact on behavior, cardiometabolic biomarkers, and medical expenditure.

**Trial Registration:**

ClinicalTrials.gov NCT04712383; https://clinicaltrials.gov/study/NCT04712383

**International Registered Report Identifier (IRRID):**

RR1-10.2196/50378

## Introduction

In July 2022, the US Preventive Services Task Force (USPSTF) recommended that providers offer personalized health behavior interventions for improving diet and physical activity to all adults in the United States, independent of an individual’s underlying risk for cardiovascular disease [1]. Tacit within this recommendation is a recognition that Americans, generally speaking, have suboptimal lifestyle behaviors [2,3] and have an increased risk of cardiovascular disease. Less than half of all Americans engage in the recommended 150 minutes per week of moderate-intensity aerobic activity or 75 minutes/week of vigorous physical activity, and only 12.3% and 10% of 294,566 surveyed adults in the United States meet the recommended daily intake of fruit or vegetables, respectively [4,5]. It is estimated that half of all American adults (117 million individuals) have at least 1 or more chronic diseases [4,6] and cardiovascular disease is the number 1 cause of death and disability [7,8]. Evidence suggests that chronic disease incidence and progression are accelerated by suboptimal health behaviors [9-12]; conversely, improving lifestyle behaviors can prevent the onset of chronic disease or modify its trajectory [13-18].

Strong evidence for the ability of an intervention to improve multiple lifestyle behaviors and prevent or delay disease onset comes from the literature surrounding the Diabetes Prevention Program, which focuses interventions among the population with prediabetes and has demonstrated as much as 30% to 60% reduction in the incidence of diabetes [19-21]. Additionally, scaling up the Diabetes Prevention Program required significant support from the Centers for Disease Control and Prevention, including increasing workforce expansion to implement the program cost-effectively, standardizing program implementation to assure quality, providing infrastructure resources to build sites that can provide the program, and developing a network to increase referrals for use of the prevention program [20,21]. However, the translation of these effects for a more generalized population is not well established [20,21]. Certainly, extending this model to all adults, independent of their risk of chronic disease, would require a huge financial and logistical undertaking, which may not be feasible.

Digital behavior change interventions (DBCIs) use mobile apps, wearables, computer programs, or websites to prevent disease through health behavior promotion and hold promise to overcome resource and time limitations that traditional behavioral interventions programs face [22-24]. Indeed, digitization of the Diabetes Prevention Program has demonstrated similar treatment effects [25-27]. Efforts to evaluate the feasibility of implementation and maintenance of in-person and digital diabetes prevention program are underway and will provide critical insight for scaling up implementation of digital approaches [28,29]. Whether the success of a digital Diabetes Prevention Program translates to the general population, that is, with and without prediabetes, remains unknown. Thus, rigorous evaluation of a holistic DBCI in the general population is needed in light of the USPSTF’s recommendation. However, investigating the effects of multimodal intervention on a diverse set of behaviors is difficult, and recruitment, retention, and DBCI adherence pose a challenge for conducting these types of studies in populations that are not recruited from clinics or on the basis of their underlying conditions.

Occupational settings provide a unique opportunity to engage a large proportion of the adult population in lifestyle behavior intervention and have been endorsed by the American Heart Association [30]. In addition to promoting healthy behavior among adults, wellness programs in the workplace can boost morale and improve productivity [31,32]. Additionally, DBCI programs are less likely to be disruptive in an occupational setting in comparison to traditional programs and, therefore, more likely to experience higher engagement and adherence. However, the availability of resources such as in-person coaching, room and space availability, and time off from work responsibilities constrain the ability to scale behavioral interventions.

To address these issues, we present a framework for a DBCI that integrates the Health Belief Model with proposed mechanisms of lifestyle interventions’ effect on chronic conditions as a precursor to subsequent research that will describe the primary outcomes of our innovative study. In this paper, we describe the design of the UMass Fitbit Care Study, which evaluates a multimodal DBCI provided by Fitbit among health care employees in Central Massachusetts. The primary objectives of the UMass Fitbit Care study were to evaluate the efficacy of intervention on the following (Textbox 1):

Our hypothesis is that self-reported lifestyle behaviors are going to be a proximal outcome affected by the intervention and likely to show the strongest treatment effect; cardiometabolic biomarkers will be more distal and show a modest treatment effect; and medical expenditure will be the most distal outcome and demonstrate a minimal treatment effect during the study period but may reveal a trend towards reduced expenditure among the intervention group.

The secondary objectives of the UMass Fitbit Care study were to characterize the following (Textbox 2):

Primary objectives of the UMass Fitbit Care study.Change in self-reported lifestyle behaviors on physical activity, nutrition, sleep, and mindfulness among participantsCardiometabolic biomarkers over a 12-month periodChronic disease–related medical expenditure

Secondary objectives of the UMass Fitbit Care study.Trajectories of intervention engagement over a 12-month periodDifferential engagement of the Fitbit intervention in relation to baseline behavior and comorbiditiesDifferential efficacy of interventions based on engagement

## Methods

### Study Design

The UMass Fitbit Care Study is a dual-arm, unblinded randomized clinical trial with a 12-month study period. SPIRIT (Standard Protocol Items: Recommendations for Interventional Trials) reporting guidelines were used in the development of this protocol and fulfilled the SPIRIT checklist [33]. Recruitment began in December of 2020. Participants were randomized to the intervention or control arm using a permuted block randomization that stratified based on age (40 vs ≥40) and sex to achieve a balance for those 2 demographic variables between the intervention and control groups (Figure 1). Participants were randomized 1:1 to a control arm, where participants only received their standard health and wellness benefits during the study period, or an intervention arm, where participants received their standard health and wellness benefits as provided by their employer, plus a digital behavioral change intervention through Fitbit at no cost for 1 year. The Fitbit DBCI included 5 components: a wearable health and fitness device (participant choice of Fitbit Inspire 2 tracker or Versa 3 smartwatch), a wireless weight scale (Fitbit Aria Air), the Fitbit app (provided basic tracking and goal setting functionalities), Fitbit Premium (provided additional advanced metrics and rich video content through the Fitbit app), and an on-demand human health coach (provided goal setting, action planning, and accountability support through secure, asynchronous, in-app messaging).

**Figure 1 figure1:**
[figure not shown]
UMass Fitbit Care Study design: health behavior data were collected through baseline and quarterly web-based surveys, while biometric measurements were obtained during clinic visits at baseline and at the 12-month follow-up. The exit screening phase concluded in January 2022. *US dollars.

### Study Setting and Participants

This study was conducted in Worcester, Massachusetts, with employees of UMass Memorial Health (UMMH). To be eligible, participants must have been enrolled on a UMMH-sponsored health plan, had to own a smartphone, had to be 18 years of age or older, and agreed to consent to the study (Figure 1). Participants who were pregnant at the time of enrollment, did not speak English, or were incarcerated were excluded from the study. The study had an a priori enrollment goal of up to 700 employees, which represents roughly 7.5% of the entire eligible population. The sample size for this study was derived based on the pragmatics of resource availability. All eligible employees were invited to participate in the study through electronic communication and a home mailer. To be enrolled in the study, participants had to electronically sign informed consent, fill out a baseline survey and demographics, use a self-scheduling service to pick an appointment for their initial biometric screening, and then complete said screening in person. Participants were then randomized to either the intervention arm or the control arm. Randomization was conducted using a random number generator to provide a random number of 1 or 2 for each of the study participants. A permuted block design with random block sizes was used to generate the randomization sequence. That sequence was loaded into a randomization module using a free, secure, and robust data collection platform called REDCap (Research Electronic Data Capture; developed at Vanderbilt University) so that it was readily available during the in-person screening process. Participants were asked to schedule an exit biometric screening at the end of the 12-month study period. Because this intervention being investigated is designed to help users improve their health behaviors in alignment with the advice of their health care providers and not to make medical decisions, the risk of harm to health is low. Participants were free to withdraw from the study at any time.

### Intervention

Participants in the intervention group were provided with a Fitbit tracker and scale and received assistance in creating a Fitbit account in the Fitbit app, syncing their devices, and enrolling into the study experience in the Fitbit app. Enrolling into the study experience gave each participant access to Fitbit Premium and Health Coaching.

### Fitbit DBCI Components

#### Wearable Health and Fitness Device

Intervention participants had a choice of a Fitbit Inspire 2 tracker or a Fitbit Versa 3 smartwatch. Both devices provided comparable health and fitness tracking features and capabilities, including steps, distance, energy burn, exercise, heart rate, active zone minutes (AZM; measure of moderate-to-vigorous physical activity based on the Physical Activity Guidelines for Americans), and sleep. The Fitbit Inspire 2 had a smaller, bracelet-like form factor and longer battery life (~10 days), while the Fitbit Versa 3 had a watch form factor, additional smartwatch features (built-in GPS, apps, etc.), and a shorter battery life (~6 days).

#### Wireless Scale

The Fitbit Aria Air scale provided intervention participants with a simple wireless (Bluetooth) scale that integrated with the Fitbit app for ease of weight trend tracking.

#### Fitbit App

The Fitbit app provided intervention participants with features to enhance tracking and goal setting for each of the health and fitness measures tracked by their wearable device. For example, the AZM feature in the app allowed users to see graphs of their trends in moderate-to-vigorous physical activity over time (daily, weekly, monthly, etc.) and to set personal goals for the number of AZMs to achieve in a day and a week. As another example, the sleep tracking feature allowed them to see their sleep duration, bedtime and wake-up time consistency, and time spent in different sleep stages and to see trends in these measures over time, as well as set goals for sleep duration, bedtime, and wake-up time.

#### Fitbit Premium

Participants assigned to the intervention arm also received Fitbit Premium. Fitbit Premium is a subscription membership service that provides advanced scores and rich content within the Fitbit app to enhance the participant experience. The advanced scores, included in both the sleep score and stress management score, provide additional feedback and insights to users on these dimensions of their wellness. The rich content includes hundreds of workout videos and mindfulness audio sessions, as well as healthy recipes, all designed to help users improve their health behaviors (Figure 2).

**Figure 2 figure2:**
[figure not shown]
Sample screenshots of Fitbit Premium features: rich video content including meditation videos (left) and advanced analytics including sleep score (right).

#### On-Demand Human Health Coach

Each intervention participant was paired with a personal, human health coach that provided goal setting, action planning, and accountability support for health behavior improvement across activity, nutrition, sleep, and mindfulness, with emphasis on the domains desired by the participant at any moment in time. The health coaches sent a secure, asynchronous, in-app SMS text message within a day of enrollment to each participant to start the process of creating a goal and an action plan for improving the behaviors when the participant’s motivation and confidence were greatest. For example, there might be an exchange of a few messages to determine that a particular user wanted to focus on improving sleep. The coach might help that user set a goal about a regular sleep schedule and an action plan for doing a mindfulness session before bed and not bringing electronic devices to bed (Figure 3).

The health coach then sent a message every day or every other day for the first few weeks to encourage the participant to stick with the plan and to provide support for follow-through or adjustment of the plan. The health coaches monitored core Fitbit data from the users (steps, AZMs, sleep, etc) via a dashboard to help tailor their support. The frequency of messages decreased as the participant gained self-efficacy; however, the option to increase messaging remained if the participant wanted extra support. Each participant was free to use any of the software features of the Fitbit app and Fitbit Premium as desired throughout the course of the intervention, although the health coach made recommendations on features such as workout videos, mindfulness sessions, etc that might be most helpful based on the participant’s goals, action plan, and device data. If participants were unresponsive for several weeks or requested to discontinue coaching, the health coaches archived their profiles in their dashboard and ceased sending them messages unless the participant proactively re-engaged by sending the coach a message.

**Figure 3 figure3:**
[figure not shown]
Sample screenshot of on-demand health coaching features. The participant and coach collaboratively create an action plan for stress management. The user can click on the coach’s profile to learn more about their background or click on the messaging button to chat securely and asynchronously.

### Data Collection and Management

There were four forms of data collected: (1) survey data through baseline surveys and scheduled quarterly surveys for all participants; (2) Fitbit-tracked data for those participants assigned to the intervention arm; (3) biometric data for all participants, which include anthropometric and vital sign measurements and laboratory investigations performed by Quest Diagnostics; and (4) total medical expenditure claims data abstracted by Conifer Health Solutions for all participants. Table 1 describes all the data collected as part of this study. An initial invitation to participate in the study was sent via email to a list of predetermined eligible employees. Interested participants signed up for the study by entering their email address, signing the consent form, and filling out their baseline survey and demographics and presented at an in-person biometric screening appointment performed by Quest Diagnostics staff. At this first visit for the biometric screening, participants in both the control group and intervention group were randomized and scheduled for the 4 follow-up quarterly surveys to study trends in perceptions, motivation, and confidence around improvements in health behaviors. An email was sent to participants each quarter with a link to the quarterly survey in UMass REDCap. Up to 2 reminder emails were sent to participants who did complete the survey. An additional email to all participants was sent in September 2021 to re-engage participants at the three-quarters point of the study. All survey data collection was performed using the REDCap data collection platform. SAS (SAS Institute) was used for all analyses. The final trial dataset, which consists of survey questionnaire data, Fitbit device data, Quest biometric data, and Conifer claims data, is only available to partners within the UMass Chan Department of Population and Quantitative Health Sciences who were responsible for the analysis.

**Table 1 table1:** Data collection schedule.

Events and procedures	Study period (January-December 2021)									Poststudy period
	Enrollment	Allocation	Postallocation				Close-out			
	Visit 0	Visit 1	3 months	6 months	9 months	12 months or visit 2				
Enrollment										
Informed consent	✓									
Demographics	✓									
Eligibility confirmation	✓									
Allocation		✓								
Assessment										
Biometric screening (height, weight, waist circumference, blood pressure, etc)—Quest Diagnostics		✓				✓				
Baseline survey (nutrition, exercise, sleep, and mindfulness habits)—REDCap^a^	✓									
Quarterly survey (nutrition, exercise, sleep, and mindfulness habits)—REDCap			✓	✓	✓	✓				
Two years of total medical expenditure claims data—Conifer Health Solutions								✓		
Intervention										
Onboarding survey for coaching component		✓								
Engagement data for each component of intervention		Continuous collection of device wear duration Event-based collection of app-open events, feature usage (including Fitbit Premium features), secure messages with coach, etc	Continuous collection of device wear duration Event-based collection of app-open events, feature usage (including Fitbit Premium features), secure messages with coach, etc	Continuous collection of device wear duration Event-based collection of app-open events, feature usage (including Fitbit Premium features), secure messages with coach, etc	Continuous collection of device wear duration Event-based collection of app-open events, feature usage (including Fitbit Premium features), secure messages with coach, etc	Continuous collection of device wear duration Event-based collection of app-open events, feature usage (including Fitbit Premium features), secure messages with coach, etc				
Wearable device and weight scale data		Continuous collection of wearable device data (steps, resting heart rate, sleep metrics, etc) Event-based collection of weight data	Continuous collection of wearable device data (steps, resting heart rate, sleep metrics, etc) Event-based collection of weight data	Continuous collection of wearable device data (steps, resting heart rate, sleep metrics, etc) Event-based collection of weight data	Continuous collection of wearable device data (steps, resting heart rate, sleep metrics, etc) Event-based collection of weight data	Continuous collection of wearable device data (steps, resting heart rate, sleep metrics, etc) Event-based collection of weight data				

^a^REDCap: Research Electronic Data Capture.

### Statistical Analysis

In this paper, we present descriptive statistics for baseline characteristics and overall engagement among the participants assigned to the intervention group using proportions and the mean for the distribution of categorical and continuous variables, respectively. The study will evaluate its primary objectives using intention-to-treat analysis. A 2-tailed Student *t* test for independent samples will be used to compare the mean of continuous variables, and a chi-square or Fisher exact test will be used to compare categorical variables between the intervention and control groups. Secondary objectives will be evaluated using group-based trajectory modeling to identify distinct trajectories of engagement and adherence, the association of distinct trajectories with baseline behavior and comorbidities, and performing an intervention-only analysis where the treatment effect of the intervention is evaluated across different trajectories of engagement. Additional exploratory analyses will consider accounting for possible contamination based on the self-reported use of wearable health and fitness devices among the control group participants. There are no plans to use biological specimens in ancillary studies. Data collection questionnaires can be provided upon request.

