## Results

### Baseline Characteristics

A total of 13,391 employees were eligible to enroll in the UMass Fitbit Care Study and received an email or home mailer about participating in the study. Of those invited, 758 completed consent to participate in less than 24 hours and scheduled an appointment for initial biometric screening. The follow-up rate was 75.7%, with 603 individuals attending the biometric screening and getting randomized to the intervention (n=300, 49.8%) or control group (n=303, 50.2%). Baseline characteristics of these 2 groups are provided in Table 2, and no systematic differences were observed between the 2 groups. On average, participants were 46.7 (SD 11.2) years of age. The majority of the participants were female (80.3%, n=484), White (85.4%, n=504), and non-Hispanic (90.7%, n=547). More than half (74.8%, n=440) of the participants had a baseline BMI that classified them as overweight or obese.

**Table 2 table2:** Baseline participant characteristics.

Characteristics		Intervention (n=300)	Control (n=303)	*P* value	
**Age (years), mean (SD)**		46.3 (11.0)	47.2 (11.4)	.34	
**Sex, n (%)**					.50
	Female	241 (80.3)	243 (80.2)		
**Race (intervention: n=295; control: n=295), n (%)**					.80
	White	254 (86.1)	250 (84.8)		
	Black or African American	11 (3.7)	9 (3.1)		
	Asian	20 (6.8)	22 (7.5)		
	Other	10 (3.4)	14 (4.8)		
**Ethnicity, n (%)**					.34
	Hispanic	16 (5.3)	25 (8.3)		
	Non-Hispanic	277 (92.3)	270 (89.1)		
	No answer	7 (2.3)	8 (2.6)		
**BMI classification (intervention: n=297; control: n=291), n (%)**					.56
	Underweight	3 (1.0)	2 (0.7)		
	Normal	65 (21.9)	78 (26.8)		
	Overweight	100 (33.7)	91 (31.3)		
	Obese	129 (43.4)	120 (41.2)		

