**Biometric measurements, mean (SD)**					
	Weight (lb; intervention: n=297; control: n=292)	185.5 (46.9)	178.4 (43.7)	.06	
	Height (in; intervention: n=297; control: n=291)	65.5 (3.5)	65.2 (3.3)	.26	
	BMI (kg/m^2^; intervention: n=297; control: n=291)	30.4 (7.1)	29.5 (6.7)	.12	
	Waist circumference (in; intervention: n=294; control: n=289)	37.6 (6.5)	36.4 (6.0)	.02	
	Systolic BP^a^ (mm Hg; intervention: n=297; control: n=291)	121.0 (9.6)	119.2 (10.2)	.03	
	Diastolic BP (mm Hg; intervention: n=297; control: n=291)	75.2 (8.0)	74.3 (7.9)	.17	
	HbA_1c_^b^ (%; intervention: n=297; control: n=292)	5.2 (0.6)	5.2 (0.5)	.47	
	Total cholesterol (mmol/L; intervention: n=296; control: n=291)	190.6 (38.7)	196.8 (38.0)	.05	
	HDL-C^c^ (mmol/L; intervention: n=296; control: n=292)	58.0 (14.5)	59.3 (14.7)	.29	
	LDL-C^d^ (mmol/L; intervention: n=296; control: n=292)	118.7 (34.5)	123.5 (34.6)	.10	
	TC/HDL ratio^e^ (intervention: n=296; control: n=292)	3.5 (1.0)	3.5 (1.2)	.57	

^a^BP: blood pressure.

^b^HBA_1c_: hemoglobin A_1c_.

^c^HDL-C: high-density lipoprotein cholesterol.

^d^LDL-C: low-density lipoprotein cholesterol.

^e^TC/HDL ratio: total cholesterol/high-density lipoprotein cholesterol ratio.

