## Discussion

### Overview

We describe the design, rationale, and baseline characteristics of a randomized control trial of a multimodal DBCI from Fitbit on improving lifestyle behaviors and cardiometabolic health in a general, rather than disease-specific, population. The high retention rate and balanced distribution of baseline characteristics, paired with a comprehensive assessment of the intervention’s impact on behavioral, cardiometabolic biomarkers, and medical expenditure, will allow for detailed evaluation of the intervention for primary and secondary endpoints.

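### The primary test is an unadjusted two-sample t test; adjusting for the baseline value, age stratum and sex would be more precise and would protect against the chance baseline differences already seen

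*Protocol article*

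**What the plan says.** The Statistical Analysis section of the protocol article says: "The study will evaluate its primary objectives using intention-to-treat analysis". For continuous outcomes the method begins "A 2-tailed Student" and continues "test for independent samples will be used to compare the mean of continuous variables". For categorical outcomes, "a chi-square or Fisher exact test will be used to compare categorical variables between the intervention and control groups". No covariate is named for either. The only further adjustment mentioned is an exploratory one for wearable use among controls.

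Under Study Design, participants were allocated "using a permuted block randomization that stratified based on age (40 vs ≥40) and sex". The Abstract and Table 1 show that behaviors are surveyed at baseline and quarterly, and that biometrics are taken at baseline and 12 months. For expenditure, Table 1 mentions only two years of claims.

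The Abstract describes the primary outcomes as changes. The Statistical Analysis section does not say whether the t test is applied to change scores or to 12-month values.

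The text accompanying Table 2 states that "no systematic differences were observed between the 2 groups", and the Discussion overview refers to "The high retention rate and balanced distribution of baseline characteristics".

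**The concern.** A baseline measurement of the same outcome is usually the strongest predictor of its follow-up value. A t test on 12-month values ignores it. A t test on change scores uses it with a fixed coefficient of 1, which is too large whenever the correlation is below 1 and the SDs are equal. Both give up precision that is available from data already collected.

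Precision matters here. The sample size was set by available resources rather than by a power calculation, and the Introduction expects only a modest effect on biomarkers.

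Table 2 adds a second consideration. The intervention arm starts higher on waist circumference (P=.02) and systolic BP (P=.03), both cardiometabolic measures. Given those differences, neither unadjusted comparison is centered on the true effect. Change scores lean towards the arm that started higher, through regression to the mean. Twelve-month values lean against it. Since the scale is not fixed in the analysis section, the direction of the lean is not settled either.

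**Working it through.** **Inputs from the article.** Table 2, intervention vs control:
- Waist ("Waist circumference (in; intervention: n=294; control: n=289"): 37.6 (SD 6.5) vs 36.4 (SD 6.0) in, difference d = 1.2 in.
- Systolic BP: 121.0 (SD 9.6), n=297 vs 119.2 (SD 10.2), n=291, d = 1.8 mm Hg.
- Exit biometrics: 227 vs 243. These sum to 470 against a printed total of 469, which does not affect the results.

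**Assumptions not in the article.** Equal SDs at both visits; baseline to 12-month correlation r from 0.5 to 0.8; two-sided alpha 0.05; the Table 2 differences persist among completers.

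**Step 1: reproduce the printed P values** (pooled t test).
- Waist: pooled SD 6.26; SE = 6.26 × √(1/294 + 1/289) = 0.519; t = 1.2/0.519 = 2.31; P = .021 (printed .02).
- Systolic BP: pooled SD 9.90; SE = 9.90 × √(1/297 + 1/291) = 0.817; t = 1.8/0.817 = 2.20; P = .028 (printed .03).

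Both agree. The standardized differences are 0.19 and 0.18.

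**Step 2: precision.** In units of the 12-month variance, the variance factors are 1 (12-month value), 2(1-r) (change) and 1-r² (ANCOVA).

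| r | change / ANCOVA = 2/(1+r) | 12-month / ANCOVA = 1/(1-r²) |
|---|---|---|
| 0.5 | 1.33 | 1.33 |
| 0.7 | 1.18 | 1.96 |
| 0.8 | 1.11 | 2.78 |

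For systolic BP, the SE on 12-month values is 9.90 × √(1/227 + 1/243) = 9.90 × 0.0923 = 0.914. The difference detectable with 80% power is 2.80 × SE, where 2.80 = 1.96 + 0.84. In mm Hg:

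| r | 12-month | change | ANCOVA |
|---|---|---|---|
| 0.5 | 2.56 | 2.56 | 2.22 |
| 0.7 | 2.56 | 1.98 | 1.83 |
| 0.8 | 2.56 | 1.62 | 1.54 |

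For an illustrative effect of 0.25 SD, power at r = 0.5 is 77% for either t test and 88% for ANCOVA. At r = 0.7 it is 77% (12-month), 94% (change) and 97% (ANCOVA).

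**Step 3: expected difference under no effect, given d.** It is r·d on 12-month values, -(1-r)·d on change, and 0 for ANCOVA under the same linear model.

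| Outcome | Scale | r = 0.5 | r = 0.8 |
|---|---|---|---|
| Systolic BP (mm Hg) | change | -0.90 | -0.36 |
| Systolic BP (mm Hg) | 12-month | +0.90 | +1.44 |
| Waist (in) | change | -0.60 | -0.24 |
| Waist (in) | 12-month | +0.60 | +0.96 |

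Negative values favor the intervention.

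**Step 4: conditional false-positive rate, systolic BP, change scores.** Given d, the estimate has SD 0.914 × √(1-r²). The test compares it with 1.96 times the larger unconditional SE, 0.914 × √(2(1-r)).
- r = 0.5: critical value 1.96 × 0.914 = 1.79; conditional SD 0.791; lower tail z = (-1.79 + 0.90)/0.791 = -1.13. The total rate is 13.0%.
- r = 0.8: critical value 1.96 × 0.578 = 1.13; conditional SD 0.548; lower tail z = (-1.13 + 0.36)/0.548 = -1.41. Adding the small upper tail, the rate is 8.3%.

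On 12-month values the same calculation gives 13% to 26%. For waist on change scores it gives 14.4% to 8.8%. ANCOVA stays at 5%. Shifting a unit-variance z by bias/SE would give 16.5% to 9.5% for systolic BP on change scores, but that uses the wrong variance for a conditional statement.

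**The case against.** Several points on the other side have force.

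- **The t test is valid.** Over repeated randomizations it is unbiased with nominal error. A reader might infer from Table 2 that the planned comparison is biased outright. The article does not support that: the shift is conditional on a chance imbalance and changes sign with the scale. Leaving out the stratification factors usually makes the test slightly conservative; no figure is available to size this.
- **Baseline may be used after all.** Because the Abstract speaks of changes, a reader should not infer that baseline is ignored. If change is tested, the smaller variance ratios apply (1.33 to 1.11).
- **The imbalance is ordinary.** Table 2 gives 16 P values, so 16 × 0.05 = 0.8 would be expected below .05 by chance, and two among correlated measures is unremarkable. Chance differences after randomization are not systematic ones, so the article's statement is defensible. Baseline P values are also a poor reason to adjust.
- **Balance is not offered as the reason for the t test.** A reader might connect the two, but the article never does.
- **Expenditure differs.** A pre-randomization year of claims is plausible but not stated, and a linear model of a 12-month value does not suit accumulated cost.
- **A fuller analysis plan may exist** and may name covariates. It is not shown. The point remains because the article states a specific test rather than leaving it open.

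These points limit the claim. They do not remove the precision loss, which holds on either scale and whether or not the arms are balanced.

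**Conclusion.** The point stands as one of precision and of robustness to the observed imbalance; the trial remains valid. The stated primary test adjusts for neither the baseline value nor the stratification factors, and its variance exceeds that of ANCOVA by 11% to 33% on change scores or by 33% to 178% on 12-month values. Conditional on Table 2, the systolic BP comparison is displaced by up to 0.90 mm Hg on change scores or 1.44 mm Hg on 12-month values, enough to matter for a result near the significance threshold.

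All these sizes rest on the assumed correlation and equal SDs. The conditional figures also require the full-sample differences to carry over to the completers. The case for adjustment rests on the prognostic value of baseline, not on the baseline P values.

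**What to change.** 1. State the outcome scale for each primary outcome.
2. For biomarkers and continuous behaviors, make the primary analysis a linear model of the 12-month value on arm, baseline value of the same outcome, age stratum and sex. Report the adjusted difference with its 95% CI.
3. For categorical behaviors, use logistic or ordinal regression with the same terms.
4. Keep the t test and the chi-square or Fisher tests as sensitivity analyses.
5. For expenditure, adjust for prior cost only if the two years of claims include a pre-randomization year, and use a model suited to cost data.
6. Give the prognostic value of baseline as the reason, not the Table 2 P values.

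The cost is a paragraph of analysis text and a few lines of SAS. For behaviors and biomarkers the covariates are already collected. The one real downside is timing: baseline data by arm are published and follow-up is complete, so the change must be dated and disclosed, with a statement of whether outcome data by arm had been seen.
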